## **6.2. Screen Failures**

Screen failures are defined as participants who consent to participate in the clinical study but are not subsequently randomly assigned to study treatment. A minimal set of screen failure information is required to ensure transparent reporting of screen failure participants to meet the Consolidated Standards of Reporting Trials publishing requirements and to respond to queries from regulatory authorities. Minimal information includes demography, screen failure details, eligibility criteria, and any serious adverse event (SAE).

Individuals who do not meet the criteria for participation in this study (screen failure) can be rescreened if there is a change in their eligibility.

## **6.3. Recruitment**

Each site will establish local recruitment and screening methods that operationalize protocol-specified requirements for eligibility determination in a manner that is tailored to and most efficient for the local study setting and target study population. Each site will use a variety of recruitment approaches, including direct recruitment at clinics, referrals from other providers and SARS-CoV-2 testing sites and laboratories, and use of online and social networking websites and apps. Recruitment materials will educate participants about COVID-19, transmission within households, and epidemiology in the community. *See Appendix 5.*

The proposed sites have established track records of high-quality clinical research integrated into clinical care settings; annual retention rates in clinical trials conducted in these sites exceed 90%. The sites have large COVID-19 epidemics with regulation limiting contact to reduce infectious spread.

## **6.4. Co-enrollment Guidelines**

Participants may be co-enrolled in other research studies, provided that these are observational studies only. Any other exception requires approval of the Principal Investigators; if a participant clinically worsens, such as requiring hospitalization, it is expected that an exception will be automatically granted and participation in treatment studies permitted. The study team should be consulted for co-enrollment in studies that do not meet this guidance or if there are questions about eligibility for co-enrollment. For any co-enrolled study, combined blood draws should not exceed current Red Cross phlebotomy guidance.

## 7. Treatments

Study treatment is defined as any investigational treatment(s), marketed product(s), placebo, or medical device(s) intended to be administered to a study participant according to the study protocol.

### 7.1. Treatments Administered

| Drug                          | Dosage formulation | Route of Administration | Manufacturer                                                                       | Instructions                             |
|-------------------------------|--------------------|-------------------------|------------------------------------------------------------------------------------|------------------------------------------|
| Placebo arm for Brazil |                    |                         |                                                                                    |                                          |
| Placebo pills                 | --                 | Oral                    | The placebo pills will be manufactured by the local certified pharmaceutical labs. | Take 2 tablets pills per day for 10 days |

Packaging and label: The medication will be dispensed in an otherwise-unmarked container with the study label. The container will be labeled with a unique identifier.

For the experimental interventions, the details on the dosage formulation, route of administration, manufacturer, and instruction are provided in their corresponding Appendix.

### 7.2. Risks to the Participants

#### 7.2.1. Risks Associated Administration with experimental therapies

The safety of experimental therapies for treatment of patients with COVID-19 disease is unknown. However, their side effect profiles are well described, and these drugs are generally well tolerated. This protocol is using a short loading dose, not a sustained one.

COVID-19 may regardless be associated with cardiac effects. The proposed regimens may prolong QT, resulting in arrhythmias. Participants will be screened for QT prolongation. Long-term manifestations of LPV/r and other regimens, including hepatic disease, are not likely in short term exposure.

The risks associated with administration of each experimental intervention is provided in their corresponding appendix.

#### 7.2.2. Risks Associated with COVID-19 Diagnosis

Enrollment in this protocol will not impact the public health department's advice for self-quarantine. Enrollment may improve morale during quarantine for COVID-19 infection. COVID-19 may be associated with anxiety, and the ability to monitor for LRTI and interact with study clinicians may allay anxiety.

#### 7.2.3. Management of Participants to Limit Risks of SARS-CoV-2 Transmission

To limit the transmission of SARS-CoV-2, participants will receive visits via secure Telehealth in order to limit the movement of persons with potential SARS-CoV-2 and leave clinical space free for ill patients requiring care. Also, to limit exposure in waiting rooms clinical specimens will be

| Harmonized protocol document                                                          |
|---------------------------------------------------------------------------------------|
| Short title: Outpatient Management of SARS-CoV-2 for High-Risk Adults in LMICs |

self-collected and collected by a study driver. This will also eliminate exposure of study personnel to SARS-CoV-2.

### 7.3. ***Dose Modification and Toxicity Management***

If a study therapy dose is missed, it should be taken as soon as possible. If it is less than 4 hours before the next dose, the dose should be skipped.

Modification for toxicities is discussed below. Only toxicities related to study medications provided through the study will be considered in the toxicity management section.

#### **Grade 1 or 2**

Participants who develop Grade 1 or 2 toxicity (per division of acquired immunodeficiency syndrome [DAIDS] adverse event [AE] Grading Table; see: [https://rsc.tech-res.com/docs/default-source/safety/division-of-aids-\(daids\)-table-for-grading-the-severity-of-adult-and-pediatric-adverse-events-corrected-v-2-1.pdf](https://rsc.tech-res.com/docs/default-source/safety/division-of-aids-(daids)-table-for-grading-the-severity-of-adult-and-pediatric-adverse-events-corrected-v-2-1.pdf)) that is considered to be related to the study medication may continue study treatment at the discretion of the site Investigator with close follow-up. If a participant chooses to discontinue study treatment, the site should notify the study protocol team within 7 days. These participants will remain on study, off study treatment, and have all evaluations performed.

#### **Grade 3**

- Participants who develop a Grade 3 symptomatic toxicity thought by the site Investigator to be related to study drug should have study product withheld, and the site should consult with the Core Protocol team. The participant should be reevaluated every 2 days until the AE returns to Grade  $\leq 2$ , at which time study drug may be reintroduced at the discretion of the site Investigator in consultation with the protocol team.
- Participants experiencing Grade 3 toxicity requiring permanent discontinuation of study product should be followed up weekly until resolution of the toxicity. Participants will have premature study treatment discontinuation evaluations performed. These participants will remain on study, off study treatment, and have all evaluations performed per the SoA.

#### **Grade 4**

- Participants who develop a Grade 4 symptomatic toxicity will have study product permanently discontinued, and the site should notify the Principal Investigator within 72 hours.
- Participants experiencing Grade 4 toxicity requiring permanent discontinuation of study product should be followed up weekly until resolution of the AE or return to baseline. These participants will remain on study, off study treatment, and have all evaluations performed per the SoA.

### **Specific Management of Toxicities Related to Study-Provided Drugs**

Specific management details of toxicities related to study provided drugs are provided in their corresponding appendix.

### 7.4. ***Method of Treatment Assignment***

Participants will be randomized at an equal allocation ratio between experimental intervention and control groups at the level of the individual.

|                                          |                 |
|------------------------------------------|-----------------|
| Date/version: May 19, 2020 – V1.0 | Page: 30 |
|------------------------------------------|-----------------|

| Harmonized protocol document                                                          |
|---------------------------------------------------------------------------------------|
| Short title: Outpatient Management of SARS-CoV-2 for High-Risk Adults in LMICs |

The randomization plan will be overseen by the Study Statistician. The randomization code and resulting allocation list will be generated and overseen by the Study Statistician. The list will be blocked and stratified by site and risk level.

### 7.5. **Blinding**

As there are multiple intervention regimens with different dosing schedule and route that make blinding for patients and clinicians will not be feasible. The medications are not identical-appearing and dosing is different for the active agents so blinding will operate in different ways across those involved in the study. This study will preserve blinding for the laboratory testing and study statisticians.

- The bottle of medication they receive will not identify the treatment allocation, only the number and frequency of pills to be taken. However, full blinding of patients will likely not be possible.
- While the study medication will be dispensed directly to participants, full blinding of the treating clinicians will not be feasible given that there are multiple intervention regimens.
- Laboratory testing for viral shedding will be blinded, as laboratory staff will not be informed of randomized assignment. The viral shedding endpoint of the trial is an objective one, unlikely to be altered by unmasking, should it occur.
- Study pharmacy staff will be unblinded, as they will prepare the study medication.
- The study statistician will be blinded for analysis purposes.

LPV/r and other regimens have a different dosing schedule and a different shape but study clinicians will not see the study medication, to mimic some blinding.

The participants will be blinded to their randomization group once assigned. At enrollment, the unblinded Study Pharmacist will use the randomization code revealed at the point of randomization to provide the participant with their group assignment and dispense the allocated study medication in a bottle marked with the study label. The medication and medication information, mid-nasal swabs sufficient to complete the study procedures, *DBS sampling kit, if within the sub-study*, and study instructions will be provided to the participant.

### 7.6. **Preparation/Handling/Storage/Accountability**

Drugs should be stored at room temperature, as per package insert. Records must be maintained that document receipt, release for dosing, disposal, or return to the sponsor.

### 7.7. **Treatment Compliance**

The participant will be contacted to ensure that they received the box of study supplies; were able to collect the mid-nasal swab and store it appropriately; and took their medication as prescribed. Participants will be asked to complete a survey that includes information regarding treatment administration. *In a sub-study, azithromycin and lopinavir-ritonavir concentrations via a DBS will also be evaluated.*

Consultation via Telehealth, text messaging, or telephone will be available to provide support to the participant to complete study procedures.

### 7.8. **Concomitant Therapy**

Participants will be asked about concomitant medications at the screening/baseline evaluation visit. During the study, participants will be asked to complete Surveys (Daily Survey and Exit Contact Survey) that include information regarding any medication or vaccine (including

|                                          |                 |
|------------------------------------------|-----------------|
| Date/version: May 19, 2020 – V1.0 | Page: 31 |
|------------------------------------------|-----------------|

| Harmonized protocol document                                                          |
|---------------------------------------------------------------------------------------|
| Short title: Outpatient Management of SARS-CoV-2 for High-Risk Adults in LMICs |

over-the-counter or prescription medicines, vitamins, and/or herbal supplements) that the participant receives during the study. At each contact, the Investigator should question the participant about any medication taken. Participants taking hormonal contraceptives to prevent pregnancy will be educated that they will need to use a backup form of birth control during the study period.

#### **7.9. *Treatment After the End of the Study***

No additional treatment will be provided at the end of the study.

| Harmonized protocol document                                                          |
|---------------------------------------------------------------------------------------|
| Short title: Outpatient Management of SARS-CoV-2 for High-Risk Adults in LMICs |

## 8. Discontinuation/Withdrawal Criteria

### 8.1. **Discontinuation of Study Treatment**

Study treatment will be discontinued for the following reasons:

- Hospitalization
- Requirement for prohibited concomitant medications or other contraindication to study product
- Occurrence of an AE requiring discontinuation of study product
- Request by participant to terminate study treatment

#### 8.1.1. ***Clinical reasons believed to be life-threatening by the physician, even if not addressed in section 7.2.Screening/Baseline Evaluation: Day 0/1***

Screening and enrolment will be done with the participant physically present.

**Day 0 evaluations are as follows:**

- Informed consent
- Collection of demographic information
- Collection of past and current medical conditions, including known pregnancy and/or lactation status
- Collection of concomitant medication information
- Collection of information regarding exposure to the index case
- Check of inclusion and exclusion criteria
- Collect mid-nasal swab for PCR

Eligible participants will be randomized. Participants will receive a monitoring kit at enrolment, which will include thermometer and SpO2 device. Participants will be instructed how to self-assess respiratory rate, temperature and oxygen saturation. A study driver wearing personal protective equipment will deliver and collect study related mid-nasal swabs and DBS cards as needed.

**The participant will do the following on Day 1:**

- Take study therapy (as assigned)
- Complete Daily Survey (online, telephone, or text messaging). This Survey will include confirmation of adherence to study therapy dosing and daily swab collection, concomitant medication review, and symptoms review and objective measures including SpO2, respiratory rate, temperature and pulse. In addition, the Baseline Dyspnea Index survey will be completed.

*Instructions for skin puncture and DBS sample preparation are provided in Appendix 4. A study team member will be available via Telehealth, telephone, or text messaging to provide support for completion of this study procedure.*

**Screening/Day 0 and Day 1 procedures can occur on the same day.**

The SARS-CoV-2 positive test results will be confirmed through laboratory records.

#### 8.1.2. **Day 2 Through Day 13**

The participant will do the following every day from Day 1 through Day 13, inclusive:

- Collect mid-nasal swab for PCR on Day 3, Day 5, Day 7 and Day 10. (Swab collection may be decreased to Day 5 and Day 10 in participants where multiple swabbing is not feasible.)
- Take study therapy (as assigned)

|                                          |                 |
|------------------------------------------|-----------------|
| Date/version: May 19, 2020 – V1.0 | Page: 33 |
|------------------------------------------|-----------------|

- Complete Daily Survey (online, telephone, or text messaging). This Survey will include confirmation of adherence to study therapy dosing and daily swab collection, concomitant medication review, AEs, and symptoms review and objective measures including SpO2, respiratory rate, temperature and pulse. In addition, the Transitional Dyspnea Survey will be completed.
- *If in DBS Sub-study, collect DBS samples for analysis of concentration of assigned experimental intervention at any time during this period (1 to 5 times) after study drug dosing has commenced. No more than 1 sample per day should be collected.*

A study team member will be available via Telehealth, text messaging, or telephone to provide support for completion of study procedures. The driver will collect the swabs as required.

#### **8.1.3. Days 3, 8 and 14 (+/-1 day)**

Contact with study clinician or staff will be conducted via telemedicine (Telehealth) or telephone. Participants will be clinically assessed for signs and symptoms of respiratory distress and will have in person assessment of AEs. As needed, additional contact with the study clinician or staff will be conducted at the request of the participant (e.g., if developing concerning symptoms or an adverse event) or if needed to clarify study procedures or follow-up symptoms.

#### **8.1.4. Day 14**

The participant will do the following on Day 14:

- Collect mid-nasal swab for PCR (May be omitted in participants where multiple swabbing is not feasible).
- Complete Daily Survey (online, telephone, or text messaging). This Survey will include confirmation of adherence to study therapy dosing and daily swab collection, concomitant medication review, and symptoms review and objective measures including SpO2, temperature and pulse.
  -
- *If in DBS Sub-study, collect DBS samples for analysis of concentration of assigned experimental intervention, if not already collected.*

A study team member will be available via Telehealth, text messaging, or telephone to provide support for completion of study procedures.

Clinical outcomes will be confirmed through the electronic health record, if possible.

#### **8.1.5. Day 28, 56 and 90**

Participants will be contacted on days 28, 56 and 90 to determine well-being. On day 56 a DBS may be collected to determine antibody development

#### **8.1.6. Participant Reimbursement**

Participants will be reimbursed on Day 14. No reimbursement will be provided to index cases for questionnaire completion and referral of their close contacts. No reimbursement will be provided for unscheduled Telehealth visits requested by the participants for support with study procedures.

## 9. Study Assessments and Procedures

- Study procedures and their timing are summarized in the SoA.
- Protocol waivers or exemptions are not allowed.
- Immediate safety concerns should be discussed with the sponsor immediately upon occurrence or awareness to determine if the participant should continue or discontinue study treatment.
- Adherence to the study design requirements, including those specified in the SoA, is essential and required for study conduct.
- All baseline evaluations must be completed and reviewed to confirm that potential participants meet all eligibility criteria. The Investigator will maintain a screening log to record details of all participants screened and to confirm eligibility or record reasons for screening failure, as applicable.
- Procedures conducted as part of the participant's routine clinical management and obtained before signing of the informed consent form may be utilized for screening or baseline purposes provided the procedures met the protocol-specified criteria and were performed within the time frame defined in the SoA.
- *Blood samples will only be collected as a part of a sub-study. The maximum amount of blood collected from each participant over the duration of the study, including any extra assessments that may be required, will not exceed 10 mL.*
- 

Participants who stop study product should continue study participation off study product with continued evaluations as per the SoA. The reason for study product discontinuation should be recorded.

### 9.1. Withdrawal from the Study

- A participant may withdraw from the study at any time at his/her own request or may be withdrawn at any time for the following reasons:
  - At the request of the primary care provider if he/she thinks the study is no longer in the best interest of the participant
  - Participant is judged by the Investigator to be at significant risk of failing to comply with the provisions of the protocol as to cause harm to self or seriously interfere with the validity of the study results
  - At the discretion of the Institutional Review Board/Ethics Committee or government agencies as part of their duties, Investigator, or industry supporter
- If the participant withdraws consent for disclosure of future information, the sponsor may retain and continue to use any data collected before such withdrawal of consent.
- If a participant withdraws from the study, he/she may request destruction of any samples taken and not tested, and the Investigator must document this in the site study records.
- See SoA for data to be collected at the time of study discontinuation and follow-up and for any further evaluations that need to be completed.

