## 12.2. *Populations for Analyses*

For analysis purposes, the following populations are defined and will be described in greater detail in the trial Statistical Analysis Plan:

| Population               | Description                                                                                                                                                                                |
|--------------------------|--------------------------------------------------------------------------------------------------------------------------------------------------------------------------------------------|
| Intention to Treat (ITT) | All enrolled participants who are randomized into the study: high-risk group for the primary clinical endpoint; high- and low-risk groups (separately) for the primary virologic endpoint. |
| Safety population        | All subjects who received at least 1 dose of study medication                                                                                                                              |
| PK evaluable             | Participants from the DBS Sub-study with at least 1 interpretable PK sample                                                                                                                |

DBS: dried blood spot; PK: pharmacokinetic;

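### Section 9.1 allows discretionary withdrawal from the study without requiring outcome follow-up to Day 90, so primary outcomes can go missing in a way related to prognosis and arm

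*Protocol*

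**What the plan says.** Protocol Section 9.1 concerns leaving the study, as distinct from stopping study product. Besides the participant's own request it gives three grounds:

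- Expected non-compliance: "Participant is judged by the Investigator to be at significant risk of failing to comply with the provisions of the protocol". The sentence goes on to limit this to non-compliance that would harm the participant or seriously damage the validity of the results.
- A wish from outside the trial team: "At the request of the primary care provider if he/she thinks the study is no longer in the best interest of the participant".
- Discretion, given to ethics bodies and authorities and extended by the words "as part of their duties, Investigator, or industry supporter".

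On later data, Section 9.1 says "See SoA for data to be collected at the time of study discontinuation and follow-up"; it leaves later assessments to the same Schedule of Activities (Section 2.1). That schedule has one combined column for Day 90 or early termination.

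Stopping the product alone is treated differently. Section 9 says: "Participants who stop study product should continue study participation off study product with continued evaluations as per the SoA". Section 7.3 gives the same rule for toxicity of Grades 1 to 4.

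Section 12.2 defines the ITT population as "All enrolled participants who are randomized into the study", and Section 12.3.1 bases the primary analysis on it. Under Missing Data, Section 12.3.1 expects to measure outcomes on all participants and says that a missing test result will be imputed. On masking, Section 7.5 states that "full blinding of the treating clinicians will not be feasible given that there are multiple intervention regimens".

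**The concern.** The primary endpoints in Section 4.1 are hospitalisation (or clinical worsening where no bed is available) and COVID-19 mortality up to 90 days. Both can be recorded whether or not the patient complies with treatment or procedures. A provider's view of the patient's interest, or an investigator's judgement of compliance, may be a reason to change what is done to the patient. Neither is a reason to stop learning whether the patient was hospitalised or died.

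These decisions are made after randomisation and before the outcome is known, by people who may have some idea of the arm. If they relate to tolerability or to the course of the illness, the lost outcomes are not a random sample. If losses fall mainly in an active arm and the patients were at above-average risk, that drug looks better than it is. If they fall mainly in the control arm, it looks worse.

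The damage is done at data collection. A statistical analysis plan can choose an imputation method, but it cannot recover outcomes that sites were allowed to stop collecting.

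**Working it through.** **Step 1. Sections side by side.**

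| Situation | What happens to follow-up | Where |
|---|---|---|
| Stops product, including for toxicity | Stays in the study, all evaluations | Sections 7.3, 9 |
| Withdrawn by provider, investigator or industry supporter | Refers to the schedule; one Day 90/early-termination contact | Sections 9.1, 2.1 |
| Confirmation in health records | Only where feasible | Section 10.1.2 |
| Analysis set | All randomised | Sections 12.2, 12.3.1 |
| Expected missing outcomes | None | Section 12.3.1, Missing Data |

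The second row creates the missing data that the last row does not expect. Two further items need non-compliers kept under observation: the secondary endpoint on non-adherence (Section 4.1) and the sensitivity analysis by actual treatment (Section 12.3.1).

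**Step 2. Inputs.** Section 12.1 gives a control rate of 20%, a relative risk reduction of 27.5% (hence 20% × 0.725 = 14.5%, a difference of 5.5 points), 492 per arm and two-sided 5%. No withdrawal rate is stated for this design. The 5% drop-out rate in Section 12.1 belongs to the separate target of 165 per arm for lower respiratory tract infection, and it is borrowed here only as an assumption. (The 492 itself does not reproduce; the usual formula gives about 990 per arm. That is a separate matter, and 492 is used here as stated.)

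**Step 3. Withdrawal in the active arm only, outcomes lost.** With a fraction w withdrawn at event risk r, the rate among those left is (p − w·r)/(1 − w), where p = 0.145.

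| w | r | Rate read in active arm | Bias (points) | Share of 5.5 points |
|---|---|---|---|---|
| 2% | 30% | (0.145 − 0.006)/0.98 = 14.2% | 0.3 | 6% |
| 5% | 40% | (0.145 − 0.020)/0.95 = 13.2% | 1.3 | 24% |
| 5% | 60% | (0.145 − 0.030)/0.95 = 12.1% | 2.4 | 44% |

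The risks of 30%, 40% and 60% are 1.5, 2 and 3 times the control rate. Against the active arm's own 14.5%, the last two are about 2.8 and 4.1 times.

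If the second scenario occurred in the control arm instead, control would read (0.20 − 0.020)/0.95 = 18.9%. The effect would then shrink from 5.5 to about 4.4 points.

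**Step 4. Type I error with no true effect.** Both arms are at 20%, and 5% are withdrawn from one arm. At r = 40% that arm reads 18.9%, and a two-sided 5% test rejects in about 7% of trials. At r = 60% it reads (0.20 − 0.030)/0.95 = 17.9%, with about 13% rejection.

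**Step 5. A second parametrisation.** A given share of would-be events in one arm is lost, with no true effect and 492 per arm (about 98 would-be events).

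| Share lost | Patients | Excluded: apparent risk ratio, rejection | Counted as non-events: apparent risk ratio, rejection |
|---|---|---|---|
| 5% | 5 | 0.96, 6.2% | 0.95, 6.8% |
| 10% | 10 | 0.92, 9.9% | 0.90, 12.6% |
| 20% | 20 | 0.83, 26.6% | 0.80, 37.2% |

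**Step 6. What does little harm.** If 10% of would-be events are lost in both arms, the rates read 18.4% and 13.2%. The risk ratio is then 0.721 against a true 0.725. The bias therefore comes from loss that differs between arms.

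**The case against.** Several points on the other side are correct.

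- A reader might infer that withdrawn patients drop out of the ITT primary analysis. The protocol does not say so: Section 12.2 includes everyone randomised, and Section 12.3.1 provides for imputation. The defect is a missing outcome, not an exclusion. Imputation is a limited remedy, however. Filling in from patients who stayed in the same arm gives about the same answer as leaving the withdrawn out, unless baseline covariates explain their extra risk.
- A reader might infer that any expected non-compliance suffices. It does not, because the clause is limited as described above, and Section 9.2 has ordinary lapses met by contact and counselling. The discretion given to the investigator or industry supporter carries no such limit.
- A reader might infer that deteriorating patients will be the ones withdrawn. No text says this. Section 8.1 makes hospitalisation a reason to stop treatment only, and Section 6.4 eases co-enrolment for patients who worsen, so worsening does not force an exit.
- Blinding is partial rather than absent. Under Section 7.5 bottles do not identify the allocation and study clinicians do not see the medication. Nothing shows that an outside primary care provider knows the arm.
- Follow-up is not simply cut off. The early-termination column includes a check of clinical outcomes, and health records may be used.

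Together these make serious bias less likely. They do not close the gap. An early-termination contact records status at the time of leaving, confirmation from records is optional, and no sentence requires ascertainment to Day 90 after a withdrawal that the participant did not ask for.

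**Conclusion.** The point holds as one about avoidable missing outcomes. Section 9.1 permits provider-, investigator- or sponsor-initiated withdrawal from the study, and nothing obliges the site to establish hospitalisation and vital status to Day 90 afterwards. This is at odds with Sections 7.3 and 9 and with the expectation in Section 12.3.1 that outcomes will be measured on all participants.

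The size is unknown. The central illustration is 13.2% read for a true 14.5%, or 24% of the assumed effect, with a range of 6% to 44%. It assumes withdrawal in the active arm only, a withdrawn group at well above average risk, none of their later events captured, and a 5% rate that the protocol states for a different target. Near-equal loss in the two arms would leave the risk ratio almost unchanged. A reader might take 24% as an expected bias; the documents do not support that. The change is worth making because a stated rule permits the problem and the remedy costs little.

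**What to change.** Reconcile Section 9.1 with the rule in Section 9 on patients who stop product, as regards outcome data only. Add that withdrawal initiated by a primary care provider, the investigator or the industry supporter does not end outcome follow-up. State that hospitalisation and vital status continue to be collected to Day 90, through the telephone contacts already scheduled or through health records, and enter the ITT analysis. The exceptions are withdrawal of consent by the participant, or a contrary order from an ethics committee or authority.

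The wording should leave untouched when and why study treatment stops; that is not the issue here.

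The cost is one paragraph and a few more calls. The Day 28, 56 and 90 contacts already exist (Sections 10.1.3 to 10.1.5), and no extra patients or procedures are needed.
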